#### Adverse events

Collected AE are detailed in point 10.3.1.

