### **2.7.1 Request for authorization under Article 34 of the HRA**

For the participants in the retrospective control group, we ask for permission to use the data without the patient's consent in accordance with Article 34 of the HRA [7]. In fact, we want to analyse 71 data files from patients who were admitted to the ICU within 2 years before the start of the study. The process of obtaining post-hoc consent would be extremely complex as ICU mortality can be as high as 20%. The exclusion of patients for whom we cannot obtain consent would lead to a selection bias.

The project sponsor/investigator confirms that no patient health-related data will be utilized in this study from patients that refused participation (in written or documented oral refusal) in research studies.

Important information regarding informed consent and the use of collected data:

- If the participant or representative refuses post-hoc or proxy consent, the participant will be withdrawn from the study. The data collected so far will be destroyed and will not be analysed (ClinO Art. 17, alinea 3) [8]. If a participant or representative withdraws his/her consent, the same process will apply.
- If no representative is identified and no proxy consent could be obtained, the patient will be withdrawn from the study and his/her data will be destroyed and will not be analysed. If the patient recovers his/her capacity to consent and declines to give consent, he or she will be withdrawn from the study and the procedure outlined above will apply.
- If a participant already enrolled in the study dies before consent or refusal could be obtained from him/ her or a representative, the personal health information collected may be used only if the participant has consented to the use of his/her personal health data for research purposes in an advance directive or other form.

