## **10. SAFETY**

Device deficiencies, AEs and SAEs collected, are fully investigated and documented in the safety report form and appropriate case report form (CRF) during the entire study period (from patient's informed consent until the end of the ICU stay or the end of the 15 days of follow up) [ISO 14155]. Documentation includes date of the event, treatment, resolution, assessment of seriousness and causal relationship to device and/or study procedure.

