#### **Serious Adverse Event (SAE) (Art. 2 Abs 58 MDR) [5]**

Any adverse event that led to any of the following:

- (a) death,
- (b) serious deterioration in the health of the subject that resulted in any of the following:
  - (i) life-threatening illness or injury,
  - (ii) permanent impairment of a body structure or a body function,
  - (iii) hospitalisation or prolongation of patient hospitalisation,
  - (iv) medical or surgical intervention to prevent life-threatening illness or injury or permanent impairment to a body structure or a body function,
  - (v) chronic disease,
- (c) foetal distress, foetal death or a congenital physical or mental impairment or birth defect.

Note: planned hospitalization for pre-existing condition, or a procedure required by the CIP, without a serious deterioration of the health status of the subject, is not considered an SAE.

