## 10.3 Documentation and reporting in Medical Device Category C clinical investigations

**Device deficiencies** and all **adverse events (AE)** including all **serious adverse events (SAE)** are collected, fully investigated and documented in the safety report form and appropriate CRF during the entire investigation period, i.e. from patient's informed consent until the last CIP-specific procedure, including a safety follow-up period.

- Documentation of AEs (including SAEs) by the PI includes diagnosis or symptoms, start and stop

dates of event, event treatment, event resolution, assessment of seriousness and causal relationship to MD and/or investigation procedure (Art. 32 ClinO-MD, ISO14155) [2, 4].

- Documentation of DDs by the PI includes description of event, start date, investigational device information, action taken regarding the investigational device, and whether the DD led to an AE. The Sponsor shall review all DDs and determine and document in writing whether they could have led to a SAE (DD with SADE potential) (Art 32. ClinO-MD, ISO14155) [2, 4].

The Sponsor provides the CA and the CEC with the documentation at their request (Art. 32 ClinO-MD) [4]. AEs which can be linked with the study (see point 10.3.1) will be assessed during the daily visit.

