### 10.3.1 Foreseeable adverse events/anticipated adverse device effects

As this is the first study to evaluate the safety and performance of the GS2 device in humans, we do not yet know the likely incidence of the anticipated adverse device effects. Therefore, we have listed the anticipated ADEs below, based on the risk management report performed in accordance with ISO 14971:2019. The probability of occurrence of the hazardous situation and the probability of severity level have been estimated in accordance with the residual risk assessment of the risk management report.

| Anticipated ADEs                                | Probability of Severity Level (S) | Probability of Occurrence of a Hazardous situation (O) |
|-------------------------------------------------|-----------------------------------|--------------------------------------------------------|
| Metabolic and nutritional disorders      |                                   |                                                        |
| Hypoglycemia event ( $\leq 3.2$ mmol/l)         | Negligable to critical (S1-4)     | Remote to Frequent (O2-5)                              |
| Hyperglycemia event ( $\geq 8.5$ mmol/l)        | Negligable (S1)                   | Remote to Occasional (O2-3)                            |
| Malnutrition: Short-term over-nutrition         | Minor to Serious (S2-3)           | Occasional (O3)                                        |
| Malnutrition: Short-term under-nutrition        | Minor to Serious (S2-3)           | Probable (O4)                                          |
| Malnutrition: Over-nutrition                    | Minor (S2)                        | Occasional (O3)                                        |
| Malnutrition: Under-nutrition                   | Minor (S2)                        | Occasional (O3)                                        |
| Gastrointestinal disorders               |                                   |                                                        |
| - Digestive disorder such as vomiting, diarrhea | Minor to serious (S2-3)           | Occasional (O3)                                        |

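### Section 9.2.4 refers adverse event collection to the anticipated-effects list in 10.3.1, whereas 10.3 requires all AEs and SAEs; one scope should be stated for both randomised arms

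*Protocol*

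**What the plan says.** The Protocol describes the scope of adverse event collection in several places.

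- **Section 9.2.4, under Adverse events**, consists of one sentence: "Collected AE are detailed in point 10.3.1".
- **Section 10.3.1** explains that this is the first study of GS2 in humans and that incidences are unknown, and continues: "Therefore, we have listed the anticipated ADEs below, based on the risk management report performed in accordance with ISO 14971:2019". Its table has seven rows: hypoglycaemia, hyperglycaemia, four over- or under-nutrition items, and digestive disorder.
- **Section 10.3, opening**, states that, besides device deficiencies, "all adverse events (AE) including all serious adverse events (SAE) are collected", to be investigated and documented over the whole investigation period.
- **Section 10.3, last sentence**, adds: "AEs which can be linked with the study (see point 10.3.1) will be assessed during the daily visit".
- **Section 10, opening**, reads: "Device deficiencies, AEs and SAEs collected, are fully investigated and documented in the safety report form and appropriate case report form (CRF". This does not say whether all events or only the listed ones are meant.
- **Section 10.1** defines an SAE as "Any adverse event that led to any of the following", followed by death and forms of serious deterioration. Nothing there refers to the 10.3.1 list.
- **Section 10.2** classifies each event by seriousness and relatedness. Its results include non-related AE, non-related SAE and unanticipated SADE.

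**The concern.** A list of anticipated device effects answers one question: is this event of an expected kind? Section 9.2.4 uses it to answer another: which events are collected? Under that use, an event's resemblance to a known device risk decides whether it is written down. In sections 10.1 and 10.2 relatedness is assessed after the event has been recorded.

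Three features of the trial make this matter. The trial is unblinded (6.1), so a bedside judgement about whether an event can be linked with the study may be made differently in the two arms. No data safety monitoring committee is planned (1.6), although early evidence of harm is a reason for stopping (1.6 and 2.9). And safety is a stated aim of a first study in humans, where an unlisted kind of harm is of particular interest. Such an event has to be recorded before 10.2 can class it as unanticipated.

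At stake are the AE record for events outside the seven rows and, for serious events outside them, the SAE entry with its seriousness and causality assessment.

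**Working it through.** No arithmetic decides this point. The check compares the passages and then follows example events through each rule.

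**Step 1: do the two rules differ?** The rule in 10.3 covers every AE and SAE. The rule in 9.2.4 covers the content of 10.3.1, and the only list there is the seven-row table. The table has no row for death, infection, cardiac event or organ failure. The two scopes are not the same.

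**Step 2: is 9.2.4 an isolated slip?** No. The last sentence of 10.3 points the daily visit to the same list, and 9.3.3 makes the daily visit the occasion on which AEs are entered in the eCRF. The narrow reading therefore appears twice, once inside the section that also states the broad rule.

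**Step 3: which reading do the other sections support?** Mostly the broad one.
- 10.1 defines an SAE without reference to the list.
- 10.2 has results for unrelated events.
- 10.3.2 sends all reported SAEs to the sponsor-investigator within 24 hours.
- The investigation schedule has an unrestricted row for (serious) adverse events.
- 12.3 monitors AE, SAE and device deficiency data for every subject.

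**Step 4: do those sections repair the narrow rule?** Only in part. The 24-hour rule applies to SAEs that have been reported. Section 12.1.2 names the eCRF itself as the source for AEs and SAEs, so for an event never entered that table names no separate source. A monitor with access to the hospital record would face the same two scopes when deciding whether an entry is missing.

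**Step 5: follow three illustrative events.**

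| Event | Under 10.3 with 10.1 and 10.2 | Under 9.2.4 read literally | Recorded elsewhere? |
|---|---|---|---|
| Hypoglycaemia | AE, classified | AE, listed | Yes, from glucose measurements (9.2.4) |
| Infection prolonging hospitalisation | SAE, with causality | Not listed | Daily events item in the synopsis, when possible; no seriousness or causality assessment stated for it |
| Death from an unlisted cause | SAE, with causality | Not listed | Alive status at ICU and hospital discharge (synopsis, 9.3.4) |

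The rules agree on the first event and diverge on the other two. In those two the fact of the event can still reach the database. What may be missing is the AE or SAE record with its assessment. An unlisted non-serious AE that is not among the other daily data items may be missing altogether.

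**The case against.** The strongest case on the other side is that the Protocol's operative design is already full collection. Section 9.2.4 is a one-line cross-reference that does not say only. The governing safety section states the broad rule, the classification in 10.2 makes sense only if unrelated events are recorded, and the SAE definition, reporting and monitoring are not tied to the list. The last sentence of 10.3 says which AEs are assessed at the daily visit; it does not say that others go unrecorded. On this view the text needs a small clarification.

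Much of that stands, and it rules out several stronger readings that a reader might infer.

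- **That deaths would be omitted.** They would not: alive status is collected at ICU and hospital discharge. One might take the remark in 2.7.1 that "ICU mortality can be as high as 20" per cent and compute 142 × 0.20 = 28.4 deaths among the randomised patients. That figure is an upper bound given to justify waiving consent for the historical group, and every such death would be in the vital-status fields under either rule. It does not measure a loss.
- **That most serious events would be missed.** The documents do not support this. SAEs have their own definition, 24-hour reporting and monitoring, and cardiac events, infections and organ failure are daily data items, when possible.
- **That unanticipated serious device effects cannot be captured.** They are defined in 10.1, are a result of 10.2 and fall within the prompt reporting in 10.3.2. The risk is that one is not recorded in the first place; the loss is not certain.
- **That a planned between-arm comparison is biased.** The safety outcomes in 5.4 are hypo- and hyperglycaemia, and 11.4 names no general AE comparison. One may be in the statistical analysis plan, which is not shown.

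What the objection does not remove is that two sentences in force direct staff to the narrow list, and that a site following either rule could claim compliance.

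**Conclusion.** The contradiction is real, and the wording of 9.2.4 and of the last sentence of 10.3 should be corrected. Read literally, 9.2.4 would allow unlisted AEs, and the SAE record with causality assessment of unlisted serious events, to go unrecorded or to be recorded inconsistently between the unblinded arms. Deaths and the glycaemic safety outcomes are not affected.

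The size cannot be calculated, because the Protocol gives no rate for unlisted AEs or SAEs and no indication of how often staff would apply the narrow rule. The conclusion assumes that at least some staff would take 9.2.4 or the daily-visit sentence at its word. If everyone works from the opening of 10.3, nothing is lost and only the inconsistency in the text remains. The sample size and the primary analysis are not touched. The point cannot be left to the statistical analysis plan, because it governs what is collected: an AE not recorded at the bedside may be hard to reconstruct later with its seriousness and causality.

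**What to change.** Reconcile the passages so that one collection scope holds for both randomised arms.

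1. In 9.2.4, replace the cross-reference with a statement that all AEs and SAEs are collected in the intervention and control arms as set out in 10.3.
2. State there, and in 10.3.1, that the 10.3.1 list is used only to judge whether an event is anticipated.
3. In the last sentence of 10.3, remove the restriction to events that can be linked with the study, so that the daily visit covers the same scope as the opening of that section.
4. If routine non-serious ICU events are to be exempt from AE entry, list the exemptions explicitly and identically for both arms, and keep all SAEs.

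The cost is a wording change and some additional eCRF entry at daily visits that already take place. Section 10.3 already requires that entry, so no new obligation arises. The change is best made before enrolment.

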#### Vital signs

Monitoring of the vital signs will stay the same as the routine monitoring during the study. The blood pressure, temperature, heart rate, respiratory rate, ventilation mode and the presence of CVVHDF and ECMO will be report daily in the eCRF.

### **9.2.5 Assessments in subjects who prematurely stop the clinical investigation**

For the patients prematurely withdrawn of the study, no follow up is planned. The data collected so far will be destroyed and will not be analysed (OClin Art. 17, alinea 3) [8] (see point 2.7 for more details).

### **9.2.6 Follow-up of the subjects after the regular termination of the clinical investigation**

Only duration of ICU stay, MRC score at ICU discharge, alive status and BMI at hospital discharge will be reported. No other follow-up is planned.

## **9.3 Procedures at each visit**

### **9.3.1 Screening visit**

Screening will be done once a day (Monday to Friday) with the help of the screening form. Once the screening is done, study information will be given to the includable patients or to the legal representative and a physician who is independent to the study. If the patient consent to participate to the study, he will be randomized in either the control or the intervention group. Because of the large number of patients, only the included patients will receive a study number.

### **9.3.2 Inclusion visit**

This visit will take place after written consent is obtained and randomization is done. The baseline data (from ICU admission) will be retrospectively reported in the eCRF form. Data included are: demographics and anthropometrics, date and time of hospitalisation and admission in the ICU, primary diagnosis and known chronic illness, medication as indicated in synopsis, laboratory, vitals and severity

score. The control or intervention will then start as explained in session 8.1.1 and 8.1.2.

### **9.3.3 Daily visit**

Daily manual data as well as AEs will be reported in the eCRF will be reported during daily visits.

### **9.3.4 Upon ICU leave visit**

Duration of ICU stay, MRC score at ICU discharge, alive status and BMI at hospital discharge will be reported in the eCRF.

## **10. SAFETY**

Device deficiencies, AEs and SAEs collected, are fully investigated and documented in the safety report form and appropriate case report form (CRF) during the entire study period (from patient's informed consent until the end of the ICU stay or the end of the 15 days of follow up) [ISO 14155]. Documentation includes date of the event, treatment, resolution, assessment of seriousness and causal relationship to device and/or study procedure.

### **10.1 Definition and Assessment of (Serious) Adverse Events and other safety related events**

#### **Adverse Event (AE) (Art. 2 Abs 57 MDR) [5]**

Any untoward medical occurrence, unintended disease or injury or any untoward clinical signs (including an abnormal laboratory finding) in subjects, users or other persons whether or not related to the MD.

#### **Serious Adverse Event (SAE) (Art. 2 Abs 58 MDR) [5]**

Any adverse event that led to any of the following:

- (a) death,
- (b) serious deterioration in the health of the subject that resulted in any of the following:
  - (i) life-threatening illness or injury,
  - (ii) permanent impairment of a body structure or a body function,
  - (iii) hospitalisation or prolongation of patient hospitalisation,
  - (iv) medical or surgical intervention to prevent life-threatening illness or injury or permanent impairment to a body structure or a body function,
  - (v) chronic disease,
- (c) foetal distress, foetal death or a congenital physical or mental impairment or birth defect.

Note: planned hospitalization for pre-existing condition, or a procedure required by the CIP, without a serious deterioration of the health status of the subject, is not considered an SAE.

#### **Device deficiency (Art. 2 Abs 59 MDR) [5]**

Inadequacy of a medical device related to its identity, quality, durability, reliability, safety or performance, of an investigational device, including malfunction, user errors and inadequate information supplied by the manufacturer.

Events such as malfunctions of the software in the automatized extraction data, in the glycaemia prediction, in the insulin sensitivity calculation or in the advice given will be reported as device deficiency.

#### **Malfunction (ISO14155) [2]**

Failure of an investigational device to perform in accordance with its intended purpose when used in accordance with the instructions for use or the CIP.

**Device deficiency with Serious Adverse Device Effect (SADE) potential** (Art. 80 Abs 1 letter c MDR; ISO14155) [2]

Any device deficiency that might have led to a serious adverse event if appropriate action had not been taken, intervention had not occurred, or circumstances had been less fortunate.

**Adverse Device Effect (ADE)** (ISO14155) [2]

Adverse event possibly, probably or causally related to the use of an investigational device or procedures.

**Serious Adverse Device Effect (SADE)** (ISO14155) [2]

Adverse device effect (ADE) that has resulted in any of the consequences characteristic of a serious adverse event.

**Unanticipated Serious Adverse Device Effect (USADE)** (ISO14155) [2]

Serious adverse device effect (SADE) which by its nature, incidence, severity or outcome has not been identified in the current version of the risk analysis report.

**Causal Relationship of SAE** (MDCG 2020-10/1) [36]

A causal relationship towards the medical device or the procedure of the investigation should be rated by the PI and the Sponsor as follows:

- **Not related:** The relationship to the device or procedures can be excluded.
- **Possible:** The relationship with the use of the investigational device is weak but cannot be ruled out completely. Alternative causes are also possible.
- **Probable:** The relationship with the use of the investigational device seems relevant and/or the event cannot reasonably be explained by another cause.
- **Causal relationship:** The serious event is associated with the investigational device or with procedures beyond reasonable doubt.

## 10.2 Adverse events categorization

The adverse events are categorized by the PI and the Sponsor using the following algorithm:

Does the AE meet the seriousness criteria?

- No, it is not serious
  - Is the relationship to the device or the procedure possible, probable or causal?
    - No: non-related AE
    - Yes: ADE
- Yes, it is serious: SAE
  - Is the relationship to the device or the procedure possible, probable or causal?
    - No: non-related SAE
    - Yes: SADE
- Is it anticipated (within expected type, severity and frequency of the complications)?
  - No: unanticipated SADE (USADE)
  - Yes: anticipated SADE (ASADE)

## 10.3 Documentation and reporting in Medical Device Category C clinical investigations

**Device deficiencies** and all **adverse events (AE)** including all **serious adverse events (SAE)** are collected, fully investigated and documented in the safety report form and appropriate CRF during the entire investigation period, i.e. from patient's informed consent until the last CIP-specific procedure, including a safety follow-up period.

- Documentation of AEs (including SAEs) by the PI includes diagnosis or symptoms, start and stop

dates of event, event treatment, event resolution, assessment of seriousness and causal relationship to MD and/or investigation procedure (Art. 32 ClinO-MD, ISO14155) [2, 4].

- Documentation of DDs by the PI includes description of event, start date, investigational device information, action taken regarding the investigational device, and whether the DD led to an AE. The Sponsor shall review all DDs and determine and document in writing whether they could have led to a SAE (DD with SADE potential) (Art 32. ClinO-MD, ISO14155) [2, 4].

The Sponsor provides the CA and the CEC with the documentation at their request (Art. 32 ClinO-MD) [4]. AEs which can be linked with the study (see point 10.3.1) will be assessed during the daily visit.

